### Incremental cost-effectiveness ratios calculation

Incremental effects and costs between groups will be modelled using generalized linear models. First, different distribution families and link functions will be tested and Akaike and Bayesian information criterion (AIC and BIC) will be used to decide the model that best fits the distribution of the effects (QALYs and severity of depression) and costs. Second, to select adjustment variables, socio-demographic and baseline clinical variables considered to be relevant will be tested in the models using likelihood ratio tests. All the models will be adjusted for gender, age and the propensity score. Difference in costs and effects will be calculated using the final models in each of the imputed databases and combined as per Rubin’s rules [40]. Incremental cost-effectiveness ratios will be calculated by diving the difference in costs between groups by the difference in effects.

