### Study setting and GP enrolment

GP enrolment was conducted six months before patient recruitment. GPs from the province of Barcelona were invited to participate. The University Institute in Primary Care Research Jordi Gol (IDIAP Jordi Gol), which gives technical support to every professional that works in Primary Care in the Catalan Public Health System, spread the invitation to participate in the study to all the GPs from the province of Barcelona. Furthermore, the research team contacted the Primary Care Centers with whom they had worked in previous research studies to invite them to participate.

The study is conducted in 12 primary care centers in the province of Barcelona (Spain). The participating centers have between six and 17 primary care teams (each of them consisting of a GP and a nurse) and attend to a population of 250,000 to 350,000 inhabitants. Sixty-eight GPs participated in the recruitment of patients for the study.

Prior to the study, GPs received a three hour-training on the study protocol, diagnostic criteria for depression, and national guidelines for the treatment (pharmacological and non-pharmacological) of MDD in primary care, divided into two 1.5-hour sessions. Session 1: Diagnosis and non-pharmacological treatment for MDD (active monitoring, sleep hygiene, counseling, frequency of follow-up visits, health education and low intensity psychological therapies); and Session 2: pharmacological treatment of MDD. During the study, a monthly newsletter is sent to the participating GPs to remind them of the topics presented in the training seminars and to inform them about the study progress.

At the beginning of the study, the GPs completed a questionnaire collecting the following variables: sociodemographic characteristics, job characteristics, training, attitude towards depression, interest on mental health and participation in communication groups [20].

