### Eligibility criteria and recruitment

Eligible patients are adults (≥18 years-old) who receive a diagnosis for a new episode of MDD. The following patients are excluded: those that have taken an antidepressant medication in the previous 60 days; those presenting psychotic or bipolar disorders or on antipsychotics, lithium or antiepileptics in the previous six months; those with history of drug abuse or dependency; those with cognitive impairment that prevents an assessment interview; and those who refuse to give signed consent to participate.

GPs recruit patients for the study from their daily list of patients attending the practice until they reach five patients for each group (active monitoring or pharmacological treatment). Maximum recruiting time is 12 months. For patients meeting the inclusion criteria, GPs inform them of the study’s aim and procedures during the medical visit, where a written informed consent is also obtained. GPs then refer patients for their first assessment appointment.

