### Interventions

This is a naturalistic study. GPs use their professional clinical judgment to recommend a treatment option to the patient. GPs can recommend a non-pharmacological intervention (Active Monitoring Group) or a pharmacological treatment with antidepressants (Medication Group) following their own clinical criteria and experience.

The patients in the Active Monitoring Group receive the usual treatment that the GPs perform when applying active monitoring without a pharmacological treatment. According to the Catalan guideline [13], which has been presented to all the GPs, active monitoring requires a first follow-up visit within the following 15 days. Afterwards, it recommends from six to eight follow-up visits over 10–12 weeks, where the GPs can consider low intensity psychosocial therapies such as counseling, problem-solving techniques or on-line CBT. Also, it recommends structured and supervised exercise programs of moderate intensity. As part of the stepped care model, in case the patient’s condition does not improve, the GP can intensify the treatment and initiate antidepressants.

Adherence to active monitoring is controlled through patient interviews (patients are asked the number of control visits with the GP and the recommendations to deal with depression from their GP). Also, at the end of the study, the GPs will be asked to describe the actions that were taken with patients in the Active Monitoring Group.

The patients in the Medication Group recieve the antidepressants usually prescribed in Spanish primary care at doses usually recommended according to their symptoms and characteristics. The national guidelines recommend initiating a pharmacological treatment with SSRIs (particularly with citalopram, sertraline, paroxetine or fluoxetine) in accordance with the Catalan Health Service’s recommendations following cost-effectiveness criteria [13].

Adherence to antidepressants is monitored through two methods: pharmacy records (computerized pharmacy records that register information about medication including active principle, dose and units supplied in the patient’s clinical history at the time of purchase), and patients’ self-reported adherence (with the 4-item scale developed by Morisky and colleagues [21]).

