### Propensity score calculation

The allocation of patients is done according to the GP’s decisions. Thus, it is expected to have bias, as groups could not be comparable. To minimize the bias resulting from the lack of randomization, we will use a propensity score. First, it will be evaluated where the probability of receiving active monitoring or antidepressants is affected by GP factors (socio-demographic characteristics, job characteristics, training, attitude towards depression, interest on mental health and participation in communication groups) and/or patient factors (socio-demographic characteristics, baseline severity of depression, presence of major depression according to SCID-I criteria, severity of anxiety, comorbid conditions and beliefs about medicines). Second, a logistic regression model will be used to calculate a propensity score. The dependent variable of this model will be the group (active monitoring or antidepressants) and the independent variables will be those that are associated with a higher or lower probability of receiving active monitoring or antidepressants.

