### Cost-effectiveness planes and cost-effectiveness acceptability curves

To deal with the uncertainty in the sampling distribution of the incremental cost-effectiveness ratio, resampling techniques with bootstrapping will be used. Replications will be done in each of the imputed databases and then combined. A minimum of 5,000 replications will be generated. Bias-corrected and accelerated (BCa) confidence intervals will be estimated on each of the imputed databases and then averaged [41]. Bootstrapped pairs of cost and effect differences will be plotted on cost-effectiveness planes and used to construct the cost-effectiveness acceptability curves.

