### Sample size

In cost-effectiveness studies, sample size calculations have been criticized and their usefulness has been questioned [42]. This calculation is influenced by many parameters, some of them related to costs, which must be specified a priori. However, knowledge about costs and deviations is scarce so it is required to make assumptions that affect the calculation of the sample size. Moreover, this calculation requires to decide, in advance, what the maximum acceptable incremental cost-effectiveness ratio or maximum willingness to pay will be. Again, where to put the cutoff points for these parameters is a complicated decision. Finally, it should be borne in mind that the results of the economic evaluation will be presented in cost-effectiveness acceptability curves. These curves are not based on statistical inference so the meaning of sample size calculations could be questioned again.

On the other hand, to deal with the uncertainty in the sampling distribution of the incremental cost-effectiveness ratio, it will be necessary to perform resampling techniques that require a minimum sample size. Previous experience in these randomized studies with naturalistic conditions indicates that a total of 150 patients per arm will suffice [41,43].

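### The cost and effect models and the bootstrap, as described, make no allowance for clustering by GP and centre, so uncertainty may be misstated

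*Protocol article*

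**What the plan says.** All places are in the protocol article.

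- **Structure.** *Study setting and GP enrolment* gives 12 centres and states "Sixty-eight GPs participated in the recruitment of patients for the study". Under *Eligibility criteria and recruitment*, each GP recruits "until they reach five patients for each group (active monitoring or pharmacological treatment", which is up to ten patients per GP. *Sample size* holds that "a total of 150 patients per arm will suffice".
- **Allocation and delivery.** *Propensity score calculation* says "The allocation of patients is done according to the GP’s decisions". *Interventions* has GPs recommend a treatment "following their own clinical criteria and experience", and the same GPs then manage the patient.
- **Models.** *Incremental cost-effectiveness ratios calculation* says "Incremental effects and costs between groups will be modelled using generalized linear models". Family and link are chosen by AIC and BIC. Further covariates come from socio-demographic and baseline clinical variables by likelihood ratio test. Gender, age and the propensity score are always included.
- **Bootstrap.** *Cost-effectiveness planes and cost-effectiveness acceptability curves* says "Replications will be done in each of the imputed databases and then combined", with at least 5,000 replications and BCa intervals. The unit to be resampled is not named.
- **GP-level elements.** Measured GP characteristics are candidate predictors in the propensity score. Clustering is not raised in the sensitivity analyses, the sample size section or the limitations.

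**The concern.** Patients of one GP share a prescriber who decides the treatment, delivers it and influences part of the resource use (GP and nurse visits, tests, specialist visits, medication). Patients of one centre share local practice. Costs and outcomes are therefore plausibly correlated within GP and centre, and so is treatment choice, since the article itself looks for GP factors that drive allocation. When both correlate within a cluster, a standard error that assumes independent patients is too small for the treatment contrast.

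The propensity score does not repair this. GP questionnaire items adjust for measured GP differences, but they do not correct the variance for residual within-cluster correlation.

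The stakes are higher than usual because this study expresses its uncertainty through the bootstrap. The sample size section sets aside a formal calculation and points to the acceptability curves. If the resampling ignores the structure of the data, the planes and curves inherit the error.

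**Working it through.** **The plan's own figure.** The 150 per arm comes with no alpha, power, effect size, standard deviation or ICC, so it cannot be reproduced. It is used here only for cluster sizes.

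**Inputs from the article.** 68 GPs; 12 centres; 2 × 150 = 300 patients; up to 5 patients per group per GP.

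**Inputs assumed.** The article gives no ICC. Outcome ICC is taken as 0.05 to 0.15 at GP level and 0.02 to 0.05 at centre level. Treatment ICC (how far treatment choice clusters) is taken as 0.3, with balanced arms and one-arm clusters as the extremes.

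**Cluster sizes.** 300/68 = 4.41 per GP; 300/12 = 25 per centre.

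**Formulas.** Design effect DE = 1 + (m − 1) × ICC(treatment) × ICC(outcome). True SE divided by naive SE = √DE. Coverage of a nominal 95% interval = 2Φ(1.96/√DE) − 1. If arms are balanced within cluster, DE = 1 − ICC(outcome).

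**Results at treatment ICC 0.3**

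| Level | Outcome ICC | DE | √DE | Coverage |
|---|---|---|---|---|
| GP | 0.05 | 1 + 3.41 × 0.015 = 1.051 | 1.025 | 94.4% |
| GP | 0.15 | 1 + 3.41 × 0.045 = 1.154 | 1.074 | 93.2% |
| Centre | 0.02 | 1 + 24 × 0.006 = 1.144 | 1.070 | 93.3% |
| Centre | 0.05 | 1 + 24 × 0.015 = 1.360 | 1.166 | 90.7% |

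A simulation of the naive two-group comparison (300 patients, 4,000 runs per scenario) agrees: 94.0% for GP at 0.05, 93.8% for centre at 0.02 and 90.9% for centre at 0.05. A centre-level outcome ICC of 0.10, above the range taken here, would give 86.2%.

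**Extremes**

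- *Arms balanced within GP*, outcome ICC 0.05: √0.95 = 0.975. The naive SE is slightly too large, and simulated coverage is 95.7%.
- *Every GP uses one arm only*, outcome ICC 0.15: DE = 1 + 3.41 × 0.15 = 1.51, √DE = 1.23, coverage 88.9%. The true SE is 23% larger than the naive one, so the naive SE is understated by 1 − 1/1.23 = 19%.
- *Every centre uses one arm only*, outcome ICC 0.05: DE = 1 + 24 × 0.05 = 2.20, simulated coverage 81.3%.
- *Arms balanced within centre, but a treatment effect that varies by centre* (assumed variance 0.05 SD², outcome ICC 0.05): simulated √DE 1.10, coverage 92.4%.

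**Does the quota guarantee balance?** Full quotas would give 68 × 10 = 680 patients. The plan is for 300, or 44% of that. A GP can contribute an average number of patients without filling either group, so balance within GP is possible but not assured.

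**The case against.** The strongest reply is that independence is read from silence. A generalized linear model does not exclude cluster-robust variance, the resampling unit is never stated, and a journal article commonly leaves such details to a full protocol or analysis plan that is not shown. This stands in part. A reader might infer that the article declares patients independent, or that its standard errors are wrong. The text supports neither. What it does support is narrower: it names the model class, the selection tools, the adjustment set, the number of replications, the interval type and five sensitivity analyses, and none of them touches clustering. AIC, BIC and likelihood ratio tests on an ordinary GLM presuppose independent observations. Followed as written, the plan has no step that would correct the variance.

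Second, the direction of the error is not fixed. This stands: with arms balanced within GP the naive SE is slightly conservative. Coverage of 88.9% at GP level is tempting to quote as the headline, but it needs every GP to use a single arm, which sits badly with recruitment into both groups.

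Third, measured GP factors in the propensity score may absorb some between-GP variation, and the societal costs include items that the GP does not control, such as productivity losses. Both points stand and argue for modest residual ICCs.

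A reader might also infer that a GP effect would remove unmeasured GP-level confounding. It would not, in the form proposed here. Cluster-robust variance leaves the point estimate unchanged. In a linear model, a random intercept with 4.41 patients per GP removes only the fraction 1 − √(1/(1 + m × ICC/(1 − ICC))) of the GP mean: about 0.10 at ICC 0.05 and 0.25 at ICC 0.15.

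**Conclusion.** The point holds as a likely misstatement of uncertainty, not as a demonstrated error. Patients are nested in GPs and centres, the GP both chooses and delivers treatment, and the analysis as described does nothing about it. At GP level the effect is small under the assumed ICCs. The larger exposure is at centre level, where 25 patients per cluster turn even low ICCs into a loss of about two to four percentage points of coverage. Bigger losses within these ICC ranges need clusters that use mostly one arm. Every figure rests on assumed outcome and treatment ICCs, and the sign reverses if arms are balanced within clusters and the treatment effect does not vary between them. The change is worth making because uncertainty is a main output of this study and the correction is cheap.

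**What to change.** 1. In the cost, QALY and PHQ-9 models, use GP-cluster-robust variance or a GP random intercept, and add centre indicators. If robust variance is chosen, note that likelihood ratio selection still assumes independence.
2. In the 5,000 replications, resample GPs with all their patients instead of single patients, and say so. Resampling centres is less reliable with only 12.
3. Include centre or GP in the imputation model.
4. Do not claim that steps 1 to 3 remove unmeasured GP-level confounding. That would need GP fixed effects or within-GP terms, which could be added as a sensitivity analysis.

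The cost is a few sentences of analysis text and minor programming, since each patient's GP is known from recruitment. Intervals may become slightly wider. Centre indicators take up differences in level between centres, but not a treatment effect that varies by centre.

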### Outcomes and participant timeline

The primary outcome of the study is cost-effectiveness, measured in terms of incremental cost per reduction of the severity of depression achieved and in incremental costs per quality adjusted life years (QALYs) gained. Figure 1 shows all the measures administered at each assessment visit as well as the time schedule of patients.

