**Figure 1 Fig1:**
[figure not shown]
**Schedule of enrolment, interventions and assessments.** PHQ-9 = Patient Health Questionnaire; CSRI = Client Service Receipt Inventory; BMQ = Beliefs about Medicines Questionnaire; SCID-I = Structured Clinical Interview for DSM Disorders; BIPQ = Brief Illness Perception Questionnaire; WHO-DAS 2.0 = World Health Organization Disability Assessment Schedule; BAI = Beck Anxiety Inventory; MAQ = Medication Adherence Questionnaire.

Costs are collected from a societal perspective. Use of health care resources and lost productivity are assessed using the Client Service Receipt Inventory (CSRI) [22] with a recall period of 12 months at baseline and six months at point two and close-out. We collect information on productivity losses, health tests, hospital care (emergency visits and stays), secondary care (visits to psychologists, psychiatrist and other specialists), primary care (visits to GP and nurse), medication use and social care services (visits to social worker). Information on the use of psychotropic medicines (active principle, dose and units supplied) is also collected from computerized pharmacy records.

The unit costs of public healthcare services are obtained from the Official Bulletin of the Catalan Government. Costs of privately funded services are obtained from published tariffs. The mean price per milligram of active principle is calculated using the prices of the generic versions of all the presentations as reported in the Spanish Vademecum. Productivity losses will be calculated based on the human capital approach using information on the minimum and average daily wage in Spain (INE) [23].

Changes in the severity of depression are assessed using the Patient Health Questionnaire 9-item depression module (PHQ-9) [24-26]. The PHQ-9 is a nine-item scale with items scored from 0 (not at all) to 3 (nearly every day) on nine symptoms of depression. Summed scores range from 0 (no depressive symptoms) to 27 (all symptoms occurring daily). Summed scores of 20 to 27 correspond to severe symptoms; 15 to 19 to moderately severe; 10 to 14 to moderate symptoms; 5 to 9 to mild symptoms; and 0 to 4 to minimal symptoms.

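### Baseline EQ-5D utility and prior-year cost are neither forced into the QALY and cost models nor listed for the propensity score, so baseline gaps between the GP-chosen groups may carry into the cost-effectiveness result

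*Protocol article*

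**What the plan says.** Three routes into the outcome models are described in the protocol article.

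- **Forced set** (Incremental cost-effectiveness ratios calculation): "All the models will be adjusted for gender, age and the propensity score".
- **Tested covariates** (same section): "to select adjustment variables, socio-demographic and baseline clinical variables considered to be relevant will be tested in the models using likelihood ratio tests". No variable is named.
- **Propensity score** (Propensity score calculation): the candidates are GP factors, patient socio-demographic characteristics and "baseline severity of depression, presence of major depression according to SCID-I criteria, severity of anxiety, comorbid conditions and beliefs about medicines". Of these, "the independent variables will be those that are associated with a higher or lower probability of receiving active monitoring or antidepressants".

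The models are fitted to "the distribution of the effects (QALYs and severity of depression) and costs". The primary outcome is cost-effectiveness, expressed as "incremental cost per reduction of the severity of depression achieved" and as cost per QALY gained (Outcomes and participant timeline). Under the same heading, resource use is collected with the CSRI "with a recall period of 12 months at baseline and six months at point two and close-out". The Abstract places patient measurements at baseline, six and 12 months and lists the EQ-5D among them. QALYs are built by linear interpolation between utilities.

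**The concern.** In a non-randomised comparison, the baseline value of an outcome is usually the first covariate to adjust for. Here the plan sets out its covariate lists, and the baselines of two of the three modelled outcomes, utility and cost, appear in none of them.

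For QALYs the problem is partly arithmetic. Baseline utility is a component of the QALY total, so a group that starts higher accrues more QALYs even if treatment does nothing. For costs, heavy users of care before the index visit tend to remain heavy users after it.

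Cost per QALY is part of the primary outcome. Suppose patients with lower utility and higher prior cost were more often given antidepressants. Both residual errors would then point the same way, towards fewer QALYs and higher cost on antidepressants, and active monitoring would look better than it is. That direction is an assumption; the documents do not state it.

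**Working it through.** **The plan's own figure.** There is none to reproduce for this point. The Sample size section gives 150 per arm without an effect size, SD, error rate or power, and the point does not depend on it. It is used below only to set n = 2 × 150 = 300.

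**Step 1: which route is open to each baseline value?**

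- *Baseline PHQ-9:* not forced. It is a propensity-score candidate as baseline severity of depression, kept if associated with group. It is also eligible for the likelihood ratio step as a clinical variable.
- *Baseline EQ-5D utility:* not forced and not a propensity-score candidate. It can enter through the likelihood ratio step only if someone classes it as clinical and relevant.
- *Prior 12-month CSRI cost:* not forced and not a propensity-score candidate. Read literally it is neither socio-demographic nor clinical, so the likelihood ratio step does not offer it either.

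None of the five listed sensitivity analyses adds baseline utility or cost. The fourth removes the propensity score and so adjusts less.

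**Step 2: weight of baseline utility in the QALY.** With linear interpolation at 0, 0.5 and 1 year:

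QALY = 0.5 × (U0 + U6)/2 + 0.5 × (U6 + U12)/2 = 0.25·U0 + 0.50·U6 + 0.25·U12.

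With no treatment effect, a baseline gap g of which a fraction r persists at both follow-ups gives a QALY difference of g × (0.25 + 0.75r). The documents give neither g nor r, so both are assumed:

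- g = 0.02: 0.005 directly (r = 0); 0.0095 at r = 0.3; 0.0125 at r = 0.5
- g = 0.05: 0.0125; 0.024; 0.031
- g = 0.10: 0.025; 0.0475; 0.0625
- g = 0.15: 0.0375; 0.071; 0.094

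These are differences before any adjustment. A propensity score removes the part of the gap that its variables share.

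**Step 3: what may remain after propensity adjustment.** This was simulated with 1,000 runs, n = 300 and a true treatment effect of zero. Assumed inputs:

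- allocation log-odds of 0.6, −0.4 and 0.4 per SD of baseline PHQ-9, utility and cost
- correlation with PHQ-9 of −0.5 for utility and 0.3 for cost
- utility SD 0.25
- slope of follow-up on baseline 0.5
- linear models, with a propensity score built on PHQ-9 alone and entered as a covariate

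Results, antidepressants minus active monitoring:

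- *QALYs:* the mean baseline utility gap was −0.154, which unadjusted implies −0.154 × (0.25 + 0.75 × 0.5) = −0.096. With the propensity score −0.044 remained, about 46% (0.044/0.096). With baseline utility added it was 0.000.
- *Cost:* +0.17 SD with the propensity score; about 0.00 SD with baseline cost added.
- *PHQ-9 change:* −0.37 SD with no adjustment; 0.00 SD with the propensity score; 0.00 SD with baseline PHQ-9 added as well.

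At the 5% level the likelihood ratio test kept baseline utility and baseline cost in every run in which they were offered. It kept baseline PHQ-9 in 20% of runs, because the propensity score already carried it.

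**The case against.** The strongest reply has four parts.

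*The propensity score may carry much of the gap.* Its candidates include depression severity, SCID-I diagnosis, anxiety and comorbidity, which overlap with several EQ-5D domains. The simulated score used PHQ-9 alone and let utility and cost drive allocation, so it probably overstates what would remain. This stands as a limit on size. It does not close the gap, because nothing ensures that the listed variables capture all of the utility difference, and prior cost is further from them.

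*Baseline utility could enter as a relevant clinical variable.* It could, and the test would very likely keep it. But this depends on a later judgment, and the same reading hardly stretches to prior cost.

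*An article condenses.* A fuller plan may name the covariates. However, the article does state a forced set and a propensity list, and a reader must take them as the plan.

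*Stronger readings do not hold.* A reader might infer that baseline PHQ-9 differences pass straight into the PHQ-9 result. For example, an assumed 3-point gap with a slope of 0.4 to 0.5 gives (1 − slope) × 3 = 1.5 to 1.8 points. That is a figure before adjustment. Severity is a named propensity-score candidate, the Discussion expects it to drive allocation, and the score is in every main model. A reader might also infer that likelihood ratio testing would discard utility or cost by chance; the simulation does not bear that out. Nor does the Discussion predict gaps in utility or prior cost: it speaks only of severity.

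**Conclusion.** The point holds for utility and cost. As written, prior cost has no route into the cost model, and baseline utility reaches the QALY model only by discretion. Any baseline gap not shared with the propensity-score variables may carry into incremental QALYs and costs, and so into the primary ratio.

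The 0.25 weight follows from the assessment times and the interpolation. The gap sizes, the 30% to 50% persistence and every simulation input are assumptions, so the example figures show scale and do not forecast the trial's bias. They also describe differences on the natural scale; a model with another link would express them differently.

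For PHQ-9 the bias is likely small. What remains is that baseline severity enters by data-driven selection. It would matter if the association screen dropped severity or if the score were entered in the wrong functional form.

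**What to change.** Amend the sentence on forced covariates so that, beside gender, age and the propensity score:

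- the QALY model always contains baseline EQ-5D utility;
- the cost model always contains the CSRI cost of the 12 months before baseline, which spans the same length of time as the follow-up cost;
- the PHQ-9 model always contains baseline PHQ-9, mainly for precision and robustness.

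Likelihood ratio testing can stay for further covariates.

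The CSRI covers the prior year at baseline, and the EQ-5D and PHQ-9 are baseline measures, so the change needs no new data or visits. Its only cost is analysis wording, and it should be made before the outcome data are analysed.
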